## Abstract

Pulmonary rehabilitation (PR) is the bedrock of non-pharmacological treatment for people with COPD. Nonetheless, it is well described in the literature that unless the patient changes his behaviour, the benefits of PR programmes will decline in six to twelve months after finishing the programme. Therefore, maintenance programmes can address the problem of PR programmes’ effect loss over time.

Community care units can provide multidisciplinary care in the current Portuguese primary health care context. These units have an interdisciplinary team that aims to develop competencies in COPD patients to self-manage the disease.

This study aims to test the effectiveness of a 12-month home-based PR programme (Rehab2Life) compared to usual care through a single-blind randomised controlled trial with two parallel groups. The Rehab2Life programme includes two distinct phases. The first is an 8-week PR programme delivered to both groups, and the second is a PR maintenance programme delivered to the intervention group after the initial eight weeks. The control group receive the usual care and regular appointments. The primary outcome is functional capacity, and secondary outcomes are dyspnea, Health-Related Quality of Life (HRQoL), number of exacerbations, symptoms burden, anxiety and depression symptoms, and physical activity.

We expect to observe that the home-based PR programme brings clinically relevant benefits to the participants at the end of the first eight weeks and that, at 12 months after the maintenance phase of the programme, benefits are less dissipated than in the control group. We expect to identify the characteristics of the patients who benefit the most from home-based programmes.

The trial was registered on 7 April 2022 at ClinicalTrials.gov (NCT05315505).

## Introduction

Pulmonary rehabilitation (PR) is the cornerstone of non-pharmacological interventions for individuals dealing with the challenges of living with chronic obstructive pulmonary disease (COPD). PR’s key elements are exercise training, patient-directed education, smoking cessation support, disease self-management, and behaviour change, which are recommended as mandatory in standard COPD PR programmes. Moreover, PR has shown the ability to improve dyspnea and enhance exercise tolerance while evaluating and dealing with specific modifiable traits that can positively affect health-related quality of life (HRQoL) [1–4]. However, there is generally low access to PR programmes due to a lack of resources or referrals to these programmes [1–3]. Despite geographical disparities in the United States of America, overall, less than 4% of COPD patients have access to PR; in Canada, this is less than 1% [4]. Reporting to Europe, the problem remains [3], and in Portugal, only 2% of COPD patients have access to PR programmes. This scarcity might be attributed to impediments such as the absence of convenient access to specialised centres and geographical discrepancies [6, 8].

Exercise training and patient education in PR have been widely studied and are recommended by several guidelines and scientific societies [5–10]. However, self-management education and behavioural transformation often do not receive the attention they deserve from healthcare practitioners. It is paramount that specific treatable attributes, such as enduring breathlessness, exacerbations, and behavioural and social risk factors, occupy a pivotal position within any comprehensive PR regimen [3, 4].

The cardinal aspiration in managing chronic diseases is empowering patients to navigate their symptoms, treatments, and lifestyle alterations efficiently. Paradoxically, the means to instigate this empowerment remains obscure. Perceived health status and self-efficacy are essential for successful participation in PR programmes. These factors are crucial for developing the skills and knowledge needed to self-manage the disease, and they can often be the most difficult to address [11–13].

The PR programme’s benefits tend to wane after six months due to patients’ failure to adopt necessary behaviour changes [14–16]. Developing self-efficacy perception and self-management skills of the disease are vital issues to change patients’ health-related behaviours [5, 14, 17]. . However, this strategy alone has proven ineffective for all patients. Incorporating behavioral change techniques, such as physical activity diaries, is paramount to enhance the effectiveness of health interventions. These diaries can provide personalised and daily goals for each patient, ensuring a more effective path to change [18]. Therefore, action is needed to ensure that, after finishing PR programmes, patients will maintain disease control behaviours throughout time, their functionality level, and their health-related quality of life [19].

In response to the challenge of diminishing PR effects over time, the concept of PR maintenance programmes emerged as a promising solution [20–23]. It is also suggested that these programmes should be offered in a home-based setting, particularly to severe patients, for twelve or more months and should be supervised [24].

In the current Portuguese primary health care context, community care units can provide multidisciplinary care to patients with COPD. These units have a multidisciplinary team, including nurses specialists in rehabilitation, whose competencies enable prescribing and delivering PR programmes, as certified by the Portuguese Order of Nurses [25]. These community care units are geographically well-distributed across the country [26].

Therefore, rehabilitation nurses have an essential role in developing structured and multidisciplinary PR programmes that may achieve the needs of patients, even the most severe patients whose functional limitation is more pronounced and those more complex due to multimorbidity [27, 28].

### Objectives

The study aims to test the effectiveness of a 12-month home-based PR programme (the Rehab2Life programme) in maintaining functional capacity, health-related quality of life, impact of the disease and physical activity after a PR programme.

### Methods and analysis

Our study is a randomised controlled trial with two parallel groups. The Rehab2Life programme includes two distinct phases. The first is an 8-week PR programme delivered to both groups, and the second is an additional PR maintenance programme given to the intervention group.

### Study setting

The study will occur in four community care units in a Portuguese urban area. All participants will undergo an 8-week home-based PR programme, after which one group will remain in a maintenance programme (intervention group). The other will have access to usual care (control group). Figure 1 – Flow diagram.

**Fig. 1 Fig1:**
[figure not shown]
Study flow diagram

### Eligibility criteria

Patients classified as B or E, according to GOLD criteria (previously B, C and D) [23], residents in the area covered by the institution where the study is carried out will be eligible for inclusion.

We will exclude patients according to Portuguese General Directorate for Health guidelines, namely: History of a PR programme in the previous six months; Patients with a COPD exacerbation within the last week; Presence of unstable comorbidities such as comorbidities that limit exercise training: ischemic cardiopathy, unstable angina, severe aortic stenosis, hypertrophic cardiomyopathy, uncontrolled arrhythmia, decompensated congestive heart failure, uncontrolled diabetes, severe cognitive dysfunction or severe psychiatric disease interfering memory and adherence [29]; Score of the Clinical Frailty Scale 2.0 above six or above five in case of not having a responsible caregiver and living alone [30, 31] and oxygen saturation level (SpO_2_) below 85% in the 6-minute walk test [29].

We will include COPD patients referred by physicians to PR. After the referral and before the inclusion in the study, patients will be evaluated by a multidisciplinary rehabilitation team to assess clinical and safety conditions to perform home-based exercise training [29].

### Recruitment

The study will be presented to health professionals in primary care, pulmonology and internal medicine departments to promote referral to PR. A short training session will be given to remind health professionals about the benefits of PR and the importance of early and adequate referral.

### Assignment of interventions

After the patient’s informed consent, allocation concealment will be ensured by opening a well-sealed envelope. The trial was registered on March 21st 2022 at ClinicalTrials.gov (NCT05315505), and this protocol is reported according to the SPIRIT guidelines.

Outcomes will be measured at four time points (T0, T1, T2 and T3) with a cardiopulmonary technician, who will not be aware of the group allocation. Every assessment will take place in the regional hospital.

The first assessment (T0) will occur before the initial PR programme. After eight weeks, the subjects will be reassessed at T1 during randomisation. At seven months, corresponding to the intermediate period of the maintenance PR programme, the subjects will be reassessed at T2 and T3 at 12 months, corresponding to the end of the study.

### Intervention

Rehabilitation nurses are specialised nurses with background education in PR. Moreover specific training on the programme’s contents was given to them with the aim of uniformising protocol implementation.

The initial home-based PR programme will have two home visits every week. Every home visit will include a personalised educational intervention, supervised exercise training, self-management and self-efficacy strategies.

The additional maintenance PR programme consists of home visits once a week for eight weeks, then home visits or phone calls once a week (alternated) for 16 weeks, and finally, home visits once a month and phone calls once every other week for 20 weeks (Fig. 2). Supervised exercise training will be conducted during home visits, validating the person’s knowledge and skills.

The intervention (Fig. 2) was designed after extensive literature review and external validation using focus groups. An exercise physiologist, a physical therapist, a specialist nurse, and a pulmonologist validated the physical exercise interventions. In addition, the educational content was validated by four specialist nurses who are widely experienced in PR programmes, and psychologists and highly experienced specialist nurses validated the self-management and self-efficacy strategies.

**Fig. 2 Fig2:**
[figure not shown]
Main contents of the PR programme

### Preparation

Before starting the Rehab2Life programme, patients go through a preparation phase in which they are taught functional respiratory re-education (FRR) techniques and issues related to awareness and motivation to perform physical exercise and changes in lifestyle habits are addressed.

FRR is essential when preparing for a PR programme in COPD patients due to limited exercise tolerance regarding their dyspnea and fatigue. FRR includes:

Teaching patients pacing and breathing techniques that can help improve exercise tolerance [32];Diaphragmatic breathing, a type of breathing that can help to improve respiratory muscle function and reduce dyspnea [33].Pursed-lips breathing (PLB), that increases functional exercise tolerance, and it is a breathing technique that involves slowly exhaling through pursed lips. It is commonly used as a management strategy for COPD [34].

Traditional patient education programmes often assume that simply providing information will lead to behaviour change. However, this program recognises a critical limitation that education alone is insufficient [35] and does not improve exercise performance [14]. This program explicitly addresses this gap and prioritises fostering awareness and willingness to change alongside knowledge acquisition. Nonetheless, patient education is a crucial component of PR programmes, as it empowers patients with the knowledge and skills to manage their condition effectively and improve their HRQoL [35, 36]. .

Education.

The key elements of the educational component are synthesised in Table 1, where we organise the components of an education programme by category and dimension [37].

**Table 1 Tab1:** Educational components of the Rehab2Life programme

Dimension	Category	Component
Self-management of COPD	Disease	COPD information
		Symptoms
		Evolution
		Importance of adapting lifestyle
		Limitations
		Travelling with COPD
		Sleep
		Sexuality
	Exacerbation	Symptoms identification
	Signs and symptoms management	Inhaled technique
		Oxygen therapy
		Dyspnoea
		Exercise intolerance
		Physical activity
		Anxiety
	Therapeutic regimen management	Smoking cessation
		Improve physical activity
		Medication
		Nutrition

This programme aims to give the patient a comprehensive understanding of COPD’s causes, symptoms, progression, and impact on daily life. Educating patients on the importance of a healthy diet and adequate hydration to support lung function and overall health is crucial to enhancing behaviour change [4, 38]. Implement evidence-based smoking cessation programmes to help patients quit smoking, as smoking cessation is essential for improving lung health and reducing the risk of complications, guiding gradually increasing physical activity and exercise, including specific exercises and modifications to accommodate COPD limitations, and equip patients with self-management skills to promote independent care and quality of life, addressing the emotional and psychological impact of COPD [4, 38].

Various educational methods include written materials, images and verbal instructions [39]. The Portuguese version of the Living Well with COPD™ is utilised [40]. The chapters are chosen according to the individual patient’s needs.

Behaviour change.

Encouraging active participation, self-reflection, and goal setting is fundamental to empowering patients and fostering motivation for behaviour change. In the Rehab2Life programme, the participants were encouraged to use goal setting to perform physical activity using an accelerometer (Yamax EX 510®) [41, 42].

In order to start the physical exercise component, some symptoms are ensured to be evaluated [5, 43, 44].

Patient assessment and monitoring:

Monitoring at the Start and End of training: Blood pressure / HR / RR / Breathing pattern;Maximum HR during training calculation: 0.80*maximum HR achieved in the 6-minute walk test;For patients on beta blockers: Maximum Borg scale 4–5 in these patients associated with 50% of the HRR. HRR: Estimated maximum HR – basal HR. (Estimated maximum HR: 220-age);BP > 160/90 mm/Hg; SpO2 < 90%; RR > 22respiratory count/min the patient does not start training;Continuous monitoring - SpO2 and HR – If LTOT, adjust to prescribed flow on exertion;If SpO2 at rest < 90% the patient does not start training.Assess the presence of dizziness, headache, fever, chest pain, and musculoskeletal pain (except mild to moderate post-workout muscle pain) – If present, the patient does not continue the training.

Physical exercise.

**Table 2 Tab2:** Exercise training components of the Rehab2Life programme

Exercise training components	
Warm Up	- Bilateral neck flexion, shoulder rotation, elbow flexion, wrist flexion/extension; - Hip and knee flexion (walking)
Endurance training	- Walking - Cycling - Stairs
Muscle strengthening	- Hip flexion/abduction and knee flexion in standing position - Seated knee extension - Squats - Full elbow flexion - Shoulder press - Push-ups on the wall
Cool-down	- Stretching the muscle groups recruited in the session

The FITT principle, which stands for Frequency, Intensity, Time, and Type, provides a framework for prescribing exercise training that effectively overloads the body. Exercise intensity for people with COPD is typically based on symptoms, and a commonly used tool is the modified Borg scale, which ranges from 0 (no exertion) to 10 (maximal exertion). A maximum exertion level of 6 on the Borg scale during exercise is often recommended in a home-based setting. Gradually increasing the duration of sessions over time is an effective way to overload the body and promote physiological adaptations. The type of exercise (Table 2) should be chosen based on the individual’s interests, preferences, availability, and safety considerations [9].

The patients must understand and monitor safety symptoms as they are motivated to perform physical exercise at least one day a week with no supervision.

The research team’s experience with COPD patients at home revealed that after finishing a centre-based program, patients often stop exercising with equipment (as most lack it at home). This leaves them with only walking and breathing exercises. To address this, we aim to give patients home tools and alternatives so they can continue the PR programme with their own resources.

Patients will be referred to a nutritionist if the Malnutrition Universal Screening Tool (MUST) score exceeds two or the Strength, Assistance in walking, Rise from a chair, Climbing stairs, and Falls score (SARC-F) exceeds four [45, 46]. The referral to a social worker will be done if the patient shows economic issues that compromise access to controlled medication, and patients will be referred to a medical doctor if there are any new exacerbation symptoms.

The programme will be interrupted in a COPD exacerbation until the condition is resolved. After being clinically stable and exhibiting minimal symptoms when compared to the usual state, the participant will receive six more supervised home PR sessions and then resume the protocol in the phase in which it was interrupted [47].

The usual care group will receive their usual medical follow-up after the initial PR programme.

All the rehabilitation nurses delivering the Rehab2Life programme have had specific training on all components of the programme, records and monitoring that must be carried out, ensuring patient safety.

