### Secondary outcomes

The secondary outcomes are dyspnea, Health-Related Quality of Life (HRQoL), exacerbations, symptoms, anxiety and depression, and physical activity.

Dyspnea will be assessed by the modified Medical Research Council (mMRC) scale [32]. This is a widely used scale with four items in which the higher the value, the greater the dyspnea intensity.

HRQoL will be assessed by the Eq. 5D [50]; The EuroQol instrument is intended to complement other quality-of-life measures and to facilitate the collection of a common data set for reference purposes.

The number of exacerbations measured by hospital admissions and emergency department visits due to COPD exacerbation will be evaluated via consultation of electronic records [51];

Symptoms will be measured by the Clinical COPD Questionnaire (CCQ) [52, 53] and the COPD Assessment Test (CAT) [54];

Anxiety and depression will be assessed by the Hospital Anxiety and Depression Scale (HADS) [55];

A pedometer (Yamax EX 510®), validated in COPD, will assess physical activity by monitoring the average daily steps [17, 41, 56]. Participants will wear the device for seven consecutive days during waking hours (except when bathing or sleeping).

Regular physical activity (p.a.) is associated with important health benefits and may prevent the development and progression of chronic diseases.

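### The Yamax EX 510 is both a goal-setting tool of the programme and the step-count instrument, so patients' reaction to it in the measured week may differ between arms at T2 and T3

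*Protocol article*

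**What the plan says.** The device appears in two places in the protocol article.

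- **As part of the intervention.** The behaviour-change text under Preparation states that "the participants were encouraged to use goal setting to perform physical activity using an accelerometer (Yamax EX 510". Here it is called an accelerometer.
- **As the outcome instrument.** Under Secondary outcomes the same model, now called a pedometer, "will assess physical activity by monitoring the average daily steps". On wear time: "Participants will wear the device for seven consecutive days during waking hours (except when bathing or sleeping".

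Physical activity is also part of the study aim. Objectives lists "impact of the disease and physical activity after a PR programme" among what the programme should maintain, and calls Rehab2Life a 12-month programme.

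On who receives what, Methods and analysis says: "The first is an 8-week PR programme delivered to both groups, and the second is an additional PR maintenance programme given to the intervention group". For controls after week 8: "The usual care group will receive their usual medical follow-up after the initial PR programme".

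On blinding, Assignment of interventions says: "Outcomes will be measured at four time points (T0, T1, T2 and T3) with a cardiopulmonary technician, who will not be aware of the group". Main potential biases concedes that the intervention itself is unlikely to be blinded.

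**The concern.** Setting activity goals with a step counter presupposes that the wearer looks at the count. If the same device is then worn in the same way to measure the outcome, the measurement can change what is measured: a patient who sees the count may walk more that week. If both arms reacted equally, the between-arm comparison would not be distorted. The worry is that they need not react equally at T2 (seven months) and T3 (twelve months), when one arm is still being visited and telephoned within the programme and the other is in usual care.

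The protections in the plan do not reach this. A technician unaware of allocation guards against observer bias, but this reaction occurs in an unblinded patient at home. Main potential biases argues that a one-year follow-up will outlast any Hawthorne effect. That argument concerns habituation to being in a study. It does not cover a short response to a device in a seven-day window that is repeated at each assessment.

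At stake is whether a step difference at T2 or T3 can be read as a difference in maintained activity, or partly reflects how each arm behaves when measured.

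**Working it through.** **1. The passages side by side**

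| Question | What the article states | What it leaves open |
|---|---|---|
| Same device in both roles? | Yes, the same model is named | Whether a separate or masked unit is used in the outcome week |
| Who was encouraged to set goals with it? | The participants, within Rehab2Life | Which arm and which phase |
| Does this continue after T1? | Rehab2Life is a 12-month programme; Intervention lists visits, calls and supervised exercise in maintenance | Device goal setting in maintenance is not mentioned; Figure 2 is not shown |
| Who is in the programme at T2 and T3? | Intervention arm only | Whether controls keep the device |
| Who wears it for the outcome? | Participants, for seven days, without distinction of arm | Whether the count is visible |

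**2. What the bias depends on**

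Let Δ be the true programme effect on usual daily steps, and r_I and r_C the rise confined to the measured week in the intervention and control arms. Then

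expected observed difference = Δ + (r_I − r_C).

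Shared reactivity cancels. Extra walking sustained by goal setting belongs to Δ. Only r_I − r_C is bias, and it can have either sign.

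**3. The plan's own figure**

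The article gives a sample size for the primary outcome only. With f = 0.25, five covariates and two-sided 5%, N = 128 gives noncentrality 0.25² × 128 = 8 on 1 and 128 − 2 − 5 = 121 degrees of freedom, and power 0.801. So 128 reproduces, and 128 / 0.8 = 160. Half of 128 is 64 per arm; the 69 per group printed beside it is a separate matter and has no bearing here. There is no corresponding figure for daily steps.

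**4. Illustration under assumptions**

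Assume 64 analysed per arm, Δ = 0, a two-sample t test at two-sided 5% with 126 degrees of freedom, and a reactivity difference of b = |r_I − r_C| / SD. The noncentrality is b × √(64/2) = 5.657 b.

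| Assumed b | Noncentrality | Chance of p < 0.05 |
|---|---|---|
| 0 | 0 | 5% |
| 0.1 | 0.57 | 8.7% |
| 0.2 | 1.13 | 20% |
| 0.3 | 1.70 | 39% |

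In steps, with both the difference and the SD assumed:

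- 300 / 3,500 = 0.09 SD gives 7.7%.
- 500 / 3,000 = 0.17 SD gives 15.5%.
- 1,000 / 2,500 = 0.40 SD gives 61%.

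The chance is the same whichever arm reacts more. These figures show how sensitive the comparison would be. They do not estimate the bias in this trial.

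**The case against.** A reader might go further and infer that the measured week is reactive in the intervention arm only, and so biased in the programme's favour. The documents do not support that.

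- **One arm only is an inference.** Both arms receive the first eight weeks, and the goal-setting sentence is not limited to an arm or a phase. The description of maintenance does not say that device goal setting continues. Controls also wear the device for the outcome, so some reactivity is shared.
- **The direction is not settled.** Patients who use the device routinely may be used to it. Controls who put it on again only for assessment may react more, which would bias against the programme.
- **A treatment effect is not bias.** Raising activity through goal setting is part of how the programme is meant to work. Only a rise confined to the measured week is artefact, and nothing in the article shows that one will occur.
- **Masking detail may sit elsewhere.** An article commonly leaves read-out procedure to the full protocol. One model can be used sealed in one role and open in the other.

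The first three stand, and they limit the point to a possible difference in reactivity of unknown sign. The fourth stands in part: the absence of a masking rule is not itself a fault. The point rests on what the article does state, namely one device in both roles, one arm still in the programme at T2 and T3, and patients who are not blinded.

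**Conclusion.** The concern holds as a credible risk of differential measurement reactivity in one secondary outcome, average daily steps at T2 and T3. It rests on three stated facts (dual use of the device, unequal programme contact after T1, unblinded patients) and one assumption, that patients can see their counts in the outcome week. Neither size nor direction can be computed from the documents. The false-positive figures rest entirely on an assumed reactivity difference and, where expressed in steps, an assumed SD.

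The 6-minute walk test, and hence the primary comparison, is not touched. Because physical activity is named in the study objective, the point is still worth settling before the step data are interpreted. It is a cheap improvement, not a threat to the trial.

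**What to change.** 1. In every seven-day outcome window (T0 to T3), in both arms, use the device with its display sealed, and have the blinded technician open it and read the count at return.
2. State whether goal setting with the device continues after T1, and who keeps the device in each arm.
3. Use one name for the device throughout, either pedometer or accelerometer.

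There is no need to suspend goal setting in the outcome weeks. Doing so would withdraw part of the programme while its effect is being measured.

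The cost is a line or two in the assessment procedure and a seal per device. The downside is loss of device feedback during the outcome weeks. If device goal setting does run through maintenance, that is one week at T2 and one at T3, out of 8 + 16 + 20 = 44 maintenance weeks.
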